### Randomization

After baseline assessments, a blind researcher will classify patients into terciles regarding their MADRS score and number of previous depressive episodes. Subsequently, patients from each tercile will be randomly assigned to the control (C), CAE, or AEMC groups. A one-way ANOVA will test for similar initial values for MADRS scores and number of depressive episodes between groups (*P* > 0.05). The Principal Investigator will be blinded to all of the procedures to perform the randomization and analyses.

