### Outcome measures – primary outcome

The MADRS scale [28] encompasses 10 items that assess apparent and reported sadness, inner tension, sleep and appetite changes, concentration difficulties, slowness, inability to feel, and pessimistic and suicidal thoughts. Nine items are based on the patient’s report and one on the psychiatrist’s observations. The higher the score, the greater the presence of depressive symptoms; scores range from 0 to 60 [62]. The MADRS scale will be applied in the pre- and post-intervention assessments.

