### Data analysis and power calculations

The Shapiro–Wilk and Levene’s tests will be used to determine normality and variance equality, respectively. Non-normal data will be log transformed. If the transformation does not produce a normal distribution, the effect of influential points in data analyses will be tested. If influential points change the interpretation of the results, they will be manually removed. Linear mixed models having group and time as fixed factors and patients as a random factor will be performed for each outcome (MADRS, clinical outcomes, hippocampal volume, brain-derived neurotrophic factor, cardiopulmonary parameters, lipid profile, and treatment costs) and domain (especially in clinical outcomes) [85]. In case an outcome presents pre-experimental period differences between groups, determined by a regular one-way ANOVA, an ANCOVA will be implemented having pre-experimental period values as covariates, group as a fixed factor, and patients as a random factor. An intention-to-treat analysis will also be performed in case of a high incidence of missing values, using linear mixed models; the first analysis will be performed removing the missing values, while the second analysis will be performed incorporating the missing data points to determine the impact of missing values in the overall results. Whenever a significant F-value is obtained, a post hoc test with a Tukey’s adjustment will be performed. In addition, within-group (pre- to post-changes) and between-group effect sizes will be calculated using Cohen’s d [86] for each outcome. Effect sizes will be classified as small (≤ 0.49), medium (0.50–0.79), and large (≥ 0.80). Finally, the level of significance adopted in the present study for all analyses will be *P* ≤ 0.05. Data will be presented as mean ± SD. SAS 9.2^®^ software (Institute Inc., Cary, NC, USA) will be used for the statistical analyses described. Considering the importance of the control of the error rates, typical error and coefficient of variation of the assessments will be performed under test and retest conditions in a sub-sample (10 subjects).

For the primary outcome (MADRS) the verification of status of depression (depressed, partial remission, full remission) and the number of patients in remission (< 10 points MADRS) will be verified [14, 87].

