Power calculations were performed using data published by Kerling et al. [88] (effect size 0.25), who showed that an aerobic exercise program can positively change depression scores as assessed by the MADRS scale. The obtained sample size was 21 patients per group (power 0.85, alfa error 0.05, correlation between repeated measures of 0.8). Assuming a drop-out ratio of approximately 30%, we will determine 25 patients per group as appropriate.

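### Baseline adjustment depends on a baseline ANOVA: with balanced MADRS terciles the primary outcome is practically never covariate-adjusted, costing modest precision, and other outcomes change model by chance

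*Protocol article*

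**What the plan says.** The section on data analysis and power calculations sets one default model: "Linear mixed models having group and time as fixed factors and patients as a random factor will be performed for each outcome". It then adds a conditional switch: "In case an outcome presents pre-experimental period differences between groups, determined by a regular one-way ANOVA, an ANCOVA will be implemented". The ANCOVA takes the baseline value as covariate. Neither an unconditional baseline covariate nor a stratum term is named for any outcome.

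Under Randomization, "a blind researcher will classify patients into terciles regarding their MADRS score and number of previous depressive episodes", after which "patients from each tercile will be randomly assigned to the control (C), CAE, or AEMC groups". The abstract also describes patients as balanced on depression score and number of episodes. Blocking within terciles is not stated, nor how the two sets of terciles are combined. The same section then tests the result: "A one-way ANOVA will test for similar initial values for MADRS scores and number of depressive episodes between groups", with P > 0.05 expected.

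The primary outcome has two measurement times: "The MADRS scale will be applied in the pre- and post-intervention assessments". The sample-size paragraph assumes a "correlation between repeated measures of 0.8".

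**The concern.** Under randomisation any baseline difference between arms is due to chance. A significance test on it therefore says nothing about whether adjustment is needed, and a non-significant result with 25 per arm does not show that the arms are alike. The value of adjusting depends on how strongly baseline predicts outcome, not on the baseline P value.

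The rule also works against the design. The trial stratifies on baseline MADRS, which makes a significant baseline ANOVA on MADRS very unlikely, and the plan reads that as a reason not to adjust. The precision bought by stratification is then left out of the standard error of the primary analysis. Precision is scarce here, because the Discussion names the comparison of two active exercise programmes as the objective and 25 patients per arm are enrolled before dropout.

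For outcomes that were not stratified, a sizeable but non-significant gap stays unadjusted, and the reported results mix two estimators selected by chance.

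**Working it through.** The plan gives no figure for the effect of this rule, so there is none to reproduce.

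**Inputs.** From the article: three arms, 25 enrolled per arm, one pre and one post value, pre-post correlation ρ = 0.8. Assumed: equal SD before and after, complete data, normal baseline values, balanced allocation within MADRS terciles, and ρ = 0.5 to show the range. The default model is read through its group-by-time contrast, which with two time points and complete data is a comparison of change scores. The article does not name the interaction, so this is an inference.

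**1. Does the trigger fire for MADRS?** For a standard normal baseline the tercile cuts are ±0.431 and the outer tercile means are ±1.091. Between-tercile variance is (2/3) × 1.091² = 0.79, so about 21% of the variance lies within terciles. Balanced allocation therefore leaves about 21% of the unstratified variance of the baseline difference between arms. In simulation the baseline ANOVA was significant in 0 of 10,000 allocations at 25 per arm and 0 of 20,000 at 21 per arm.

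**2. Standard error of the MADRS contrast.** In units of 2σ²/n:
- variance assumed by the change-score model: 2(1 − ρ)
- variance with ANCOVA: 1 − ρ²
- true variance of the change contrast under tercile balance: (1 − ρ²) + 0.21(1 − ρ)²

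| ρ | model | true | ANCOVA | SE too wide by |
|---|---|---|---|---|
| 0.8 | 0.40 | 0.36 + 0.21 × 0.04 = 0.368 | 0.36 | √(0.40/0.368) = 1.04, i.e. 4% |
| 0.5 (assumed) | 1.00 | 0.75 + 0.21 × 0.25 = 0.803 | 0.75 | √(1.00/0.803) = 1.12, i.e. 12% |

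**3. Error rate and power for MADRS.** With balanced terciles and 21 per arm (20,000 runs), the nominal 5% test rejects under no effect in 3.9% of trials at ρ = 0.8 and 2.3% at ρ = 0.5. ANCOVA gives 4.9% and 5.0%. Power for a 0.5 SD AEMC-CAE difference, 25 per arm, unadjusted pairwise test, by simulation:

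| ρ | planned | ANCOVA |
|---|---|---|
| 0.8 | 0.78 | 0.83 |
| 0.5 (assumed) | 0.37 | 0.51 |

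**4. If allocation within terciles is not blocked.** The baseline ANOVA is then significant in about 5% of trials, and chance decides which model the primary outcome receives.

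**5. Unstratified outcomes.** The critical value is F(0.95; 2, 72) = 3.124. With arm means −d/2, 0 and d/2, F = 25 × (d²/4 + d²/4)/2 = 6.25d², so gaps up to d = √(3.124/6.25) = 0.71 SD can pass as similar in that configuration. The AEMC-CAE baseline gap has standard error √(2/25) = 0.28 SD. In simulation about 5% of outcomes have a gap of at least 0.5 SD that the ANOVA misses, and about 5% trigger the switch to ANCOVA.

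Given a baseline gap, the change contrast is shifted by (1 − ρ) × gap, in the direction opposite to the gap. For 0.5 SD this is 0.2 × 0.5 = 0.10 SD at ρ = 0.8 and 0.5 × 0.5 = 0.25 SD at ρ = 0.5. ANCOVA is shifted by about 0. Over all allocations the mean error of the two-stage estimate is about 0, and the F test rejects under no effect in 4.9% (ρ = 0.8) and 4.5% (ρ = 0.5) of trials.

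**The case against.** Four points can be made for the plan.

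- *Baseline is not ignored.* The default model has it as a response, so the contrast works on change. This stands: what is missing is the covariate, and the cost is efficiency.
- *The loss for MADRS is small and conservative at the only correlation the article gives.* This stands. The larger losses need a lower correlation, which is assumed here.
- *The near-certainty that the trigger stays silent depends on balanced allocation within terciles.* This stands. The abstract's wording supports balance, but no method is given. Without blocking, the objection becomes chance selection of the primary model.
- *Randomisation already protects the secondary outcomes.* On average it does.

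Two stronger readings are tempting. A reader might infer that the secondary results are biased. The documents do not support that without qualification: the shift is conditional on an observed imbalance and averages to zero over repeated randomisation.

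A reader might also infer that false-positive rates for AEMC against CAE are inflated. Unadjusted pairwise tests would suggest so: 8.3% (ρ = 0.8) and 11.0% (ρ = 0.5) at undetected gaps near 0.5 SD. The plan, however, requires a significant F test and then Tukey's adjustment, and under that procedure the rates are 3.3% and 4.8%. At gaps near 0.7 SD they are roughly 3–4% and 8–10%, from few runs. The F test alone is mildly inflated near 0.5 SD (6.9% and 8.2%), again only conditionally. General inflation cannot be claimed.

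**Conclusion.** The point holds as one of efficiency and consistency, and should be fixed. A test that measures only chance chooses the model for each outcome. For MADRS, if terciles are balanced, it steers the analysis away from the covariate on which the design was balanced. The size is an SE about 4% too wide and about 5 points of power at ρ = 0.8, rising to about 12% and 14 points at an assumed 0.5. For the other outcomes about 1 in 20 carries an undetected gap of at least 0.5 SD and about 1 in 20 changes model, while overall type I error stays near 5%.

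These figures rest on 25 complete patients per arm, equal SDs, and the change-score reading of the default model. The MADRS figures also need balanced allocation within terciles. The rule does not make the primary comparison invalid or anti-conservative.

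**What to change.** Delete the baseline-ANOVA trigger from the analysis section, and state that the P > 0.05 check under Randomization is not a criterion for the analysis. For every outcome measured before and after, MADRS first, prespecify adjustment for its own baseline value whatever the baseline P value. Either of two forms will do:

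- the post value regressed on group and baseline; or
- the mixed model with one common baseline mean for the three arms, which keeps patients without a post value.

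Use the same form for all such outcomes. Treatment costs are collected only over the intervention period and fall outside this rule.

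The cost is a change of wording. The baseline values are already in the assessment schedule, no extra patients are needed, and the article's trial status section reports that nobody had yet been included.

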### Type of participants

The sample will be composed of 75 patients with depression. Considering the heterogeneity of this population, the following inclusion criteria will be adopted: (1) diagnosed with major depression (single episode or recurrent episodes) as assessed by the MINI [55]; (2) pharmacological treatment for depression (use of antidepressants); (3) not engaged in regular exercise program (e.g., aerobic and/or strength training) for the 6 months prior to the commencement of experimental period; (4) absence of severe motor impairments, musculoskeletal injury, severe respiratory diseases, acute pulmonary embolism, unstable angina pectoris or severe heart failure, vascular brain disease, severe cardiopulmonary dysfunction, acute myocardial infarction or early phase of rehabilitation (critical aortic stenosis, severe hypertrophic and obstructive cardiomyopathy, untreated malignant arrhythmias, untreated severe hypertension, severe pulmonary hypertension), stroke or neurological disease, symptomatic cardiac malformations (e.g., septal defects, patent ductus arteriosus or valvular stenosis), atrioventricular block grade II or III, left bundle-branch block, or ventricular complex arrhythmias.

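### Intention-to-treat is an extra analysis run only if missing data are judged high, with no threshold and no statement of which result governs, although the plan expects about 30% drop-out

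*Protocol article*

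**What the plan says.** Under Data analysis and power calculations, the protocol article specifies linear mixed models for every outcome, with group and time as fixed factors and patient as a random factor. An ANCOVA replaces them when groups differ at baseline. It then adds: "An intention-to-treat analysis will also be performed in case of a high incidence of missing values, using linear mixed models". The same sentence goes on to describe two runs. Of one it says that "the first analysis will be performed removing the missing values"; the other takes the missing points into account, so that their influence on the findings can be judged.

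The sample-size paragraph of that section states: "Assuming a drop-out ratio of approximately 30%, we will determine 25 patients per group as appropriate". Type of participants gives the total: "The sample will be composed of 75 patients with depression". Under Outcome measures – primary outcome, MADRS is applied before and after the intervention only; the schedule under Setting places the post-intervention MADRS at Visit 9.

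Nowhere does the article define a high incidence of missing values, name a primary analysis set, or say which of the two runs decides the trial's conclusion.

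**The concern.** Intention-to-treat is normally the fixed basis of a superiority comparison. Here it is additional and conditional, and the condition is a judgement on the accumulated data. If missingness is judged not to be high, no intention-to-treat analysis is promised. If it is judged high, there are two results and no rule for choosing between them. Blinding the analyst to allocation does not remove this freedom, because the amount of missing data and the significance of each run are visible without knowing which arm is which.

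Drop-out may also be informative. The exercise arms train twice a week for 24 weeks, and the control arm has no programme to adhere to. If the arms lose different proportions of patients, and those lost differ in how much they improve, a comparison of patients with complete data no longer rests on randomisation.

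**Working it through.** **1. Expected loss, from the plan's own figures.** 3 × 25 = 75 randomised. At 30% drop-out, 0.30 × 75 = 22.5 are lost, so 22 to 23 patients. Per group, 25 × 0.70 = 17.5 remain. (The stated 21 per group divided by 0.70 gives 30, not 25; 25 covers 1 − 21/25 = 16% drop-out. That is a separate matter, and the present point does not depend on it.)

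**2. Illustrative size of the bias.** Let p be the proportion lost in an arm and D the difference in mean MADRS change between patients lost and patients retained, the same in both arms. The mean change among those retained is off by p × D, so the between-arm difference is biased by (p1 − p2) × D. The documents give neither quantity. Assuming p1 − p2 of 0.10 to 0.20 and D of 3 to 9 points:

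- low end: 0.10 × 3 = 0.3 points
- high end: 0.20 × 9 = 1.8 points

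**3. How much of this the mixed model could remove.** A patient without a post score contributes at most a baseline. With the plan's pre–post correlation of 0.8 and equal variances (assumed), the expected change falls by 1 − 0.8 = 0.2 points per point of baseline. The model corrects for lost patients only through that slope. In units of the baseline variance, cov(baseline, change) = 0.8 − 1 = −0.2 and var(change) = 2 × (1 − 0.8) = 0.4. Three cases, to first order:

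- *Drop-out driven by change.* A gap D in change implies a baseline gap of (−0.2/0.4) × D = −0.5D. The model predicts a change gap of −0.2 × (−0.5D) = 0.1D, so 0.9D is uncorrected. Applied to step 2, about 0.27 to 1.62 of the 0.3 to 1.8 points remains.
- *Drop-out driven by the post score.* A gap G in post score implies a baseline gap of 0.8G and a true change gap of 0.2G. The model predicts −0.2 × 0.8G = −0.16G, so the error is 0.36G against 0.2G without the model, which is worse.
- *Drop-out driven by baseline only.* A baseline gap B gives a true change gap of −0.2B and a predicted gap of −0.2B, so the bias is removed. Its sign is opposite to the other two cases if the patients lost are the more severely ill.

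**4. Simulation of the same three cases.** Assumed SD 8, correlation 0.8, drop-out about 36% in one arm and 16% in the other. Absolute bias in MADRS points:

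| Drop-out driven by | Missing removed | Mixed model, all available values |
|---|---|---|
| Change | 1.04 | 0.96 |
| Post score | 0.33 | 0.68 |
| Baseline only | 0.33 | about 0 |

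The simulated pattern agrees with the algebra. These sizes depend on the assumed strength of the link between drop-out and score.

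**The case against.** The strongest reply has four parts.

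*The text removes values, not patients.* This stands. In a mixed model fitted to one record per visit, removing a missing post value can leave the patient's baseline in the analysis. A reader might infer that the first run discards every incomplete patient; the wording does not establish that, although the ANCOVA fallback, which models the post value, would lose anyone without one.

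*Nothing calls that run the main analysis.* This also stands. A reader might infer from the order of the two runs that the headline comparison would be a non-randomised one among completers. The order is all the text gives, and the stated purpose of the second run is to gauge the effect of missing data. What can be said is that no primary set is named.

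*At 30% drop-out the intention-to-treat analysis would be run anyway.* Probably true, and if missingness is low the possible bias shrinks too. But the trigger stays undefined, and running both analyses does not settle which one decides.

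*Changing the model does not remove the quoted bias.* Correct, as steps 3 and 4 show. A reader might take 0.3 to 1.8 points as the gain from making intention-to-treat primary. The documents do not support that: the figure rests on assumed inputs, drop-out is given as one overall proportion and not by arm, and controls could be the ones who leave more often.

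**Conclusion.** The point holds as a defect in how the primary analysis is fixed. Intention-to-treat is conditional on an undefined trigger, judged after the data are seen, and no result is named as governing, in a plan that expects to lose 22 to 23 of 75 patients. Confidence in this is high because it rests on the wording alone.

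The harm is less certain. Bias of 0.3 to 1.8 MADRS points illustrates what differential drop-out could do under a 10 to 20 percentage-point imbalance and a 3 to 9 point gap in change. Its direction is unknown, and it would largely persist under the mixed model unless post scores are obtained from patients who stop training. Making the all-randomised analysis primary removes the choice of analysis after the fact; follow-up of those who stop is what addresses the bias. This should be fixed, but it does not by itself invalidate the trial.

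**What to change.** State that the primary MADRS analysis always includes all randomised patients in their allocated arm, however much is missing, using the linear mixed model already named with all available pre and post values. Delete the condition on a high incidence of missing values. Label the analysis with missing values removed as a sensitivity analysis and say that it does not govern the conclusion.

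State also that patients who stop training are still invited to the existing Visit 9 MADRS assessment, and that those scores enter the primary analysis.

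The cost is a few sentences of wording, follow-up calls to patients who stop training, and possibly a smaller estimated effect once their scores are included. Under Trial status the article reports that no participants had yet been included, so on that footing the change could be made before any data are seen.

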As a large portion of patients with depression do not properly respond to drug treatment (30% response without remission, 20% partial remission and 50% remission) [14], alternative interventions should be added to standard drug treatment aiming to improve the health status of patients. Non-pharmacological synergic interventions, such as physical exercise, have been deemed effective to mitigate the burden of depression and associated comorbidities [15, 16]. Accordingly, physical exercise has been widely recommended as an effective non-pharmacological intervention for depression, cognitive function, hypertension, obesity, and type 2 diabetes [17, 18]. The effectiveness of physical exercise to decrease the burden associated with these conditions has been confirmed by several systematic reviews and meta-analyses [16, 19–22]. For example, Cooney et al. [16] (35 studies, 1.353 subjects) and Wegner et al. [19] (32 studies, 48,207 subjects) reported that aerobic exercise can reduce depression symptoms (effect sizes of 0.62 and 0.56, respectively). Smith et al. [20] (31 studies, 2.049 patients with depression) demonstrated that physical exercise produces small improvements (in elderly people) in indices of cognitive function, such as attention and processing speed (effect size 0.16), executive function (effect size 0.12), and memory (effect size 0.12). Furthermore, Cornelissen and Smart [21] found a reduction in systolic blood pressure of healthy adults after aerobic exercise (93 studies, 5223 subjects).

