## Discussion

The present study has the objective to verify if patients with depression randomized into one of two physical exercise interventions (AEMC or CAE) combined with traditional drug treatment will present distinct improvements in depression symptoms (MADRS). In addition, different outcomes commonly altered by depression and with the potential to be reversed by physical exercise (e.g., cognitive function, hippocampal volume, brain-derived neurotrophic factor, sleep parameters, cardiovascular risk parameters, suicidal behavior, functionality, and treatment costs) will be evaluated.

From an operational standpoint, a pilot study involving 45 healthy elderly people was carried out in 2017, considering interventions with AEMC (two levels) and CAE (stationary cycling). Data from the pilot study are under analysis, but greater improvements with regards to cognitive and motor aspects were observed in the group undergoing exercises with greater motor complexity. In addition, training interventions produced very high exercise adherence (95%), which may be a differential, considering the difficulties in maintaining adherence during a traditional physical exercise program [89]. The main objective of this pilot study was to establish training routines and assessments and to provide logistical experiences between the parties involved (BHU, University, institutions involved in implementing training interventions and evaluations, and researchers) for the development of the proposal with patients with depression.

To our knowledge, this is the first study to test the effect of adding physical exercise to traditional treatment in patients with depression in a primary health care setting in Brazil. In addition, the use of aerobic exercises with insertion of activities with progressively higher motor complexity has not yet been tested in this population. Considering that exercises with high motor complexity may promote changes in cortical activation [90] and possibly increase the volume of associated encephalic structures (i.e., hippocampus) [27] in healthy individuals, assessing such adaptations in patients with depression is of great interest for clinical practice and public policies.

Finally, determining the impact of physical exercise programs on the treatment costs of patients with depression in Brazil may lead to new polices on how to treat them while decreasing the associated costs [2].

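### The stated inputs appear to give 21 patients in total, not 21 per group, and the 0.85 power is not shown to apply to AEMC versus CAE

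*Protocol article*

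**What the plan says.** The protocol article, under Data analysis and power calculations, states: "The obtained sample size was 21 patients per group (power 0.85, alfa error 0.05, correlation between repeated measures of 0.8". The effect size of 0.25 comes from a published study "who showed that an aerobic exercise program can positively change depression scores as assessed by the MADRS scale". The paragraph names neither the test nor the metric of the effect size, and does not give that study's comparator. It then allows for about 30% drop-out and settles on 25 patients per group.

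The design is given elsewhere. There are three groups: control, CAE and AEMC (Randomization). MADRS is taken before and after the intervention (Outcome measures – primary outcome). The analysis is a linear mixed model with group and time, with Tukey-adjusted comparisons after a significant F (Data analysis and power calculations).

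The Discussion gives the objective as whether patients "randomized into one of two physical exercise interventions (AEMC or CAE) combined with traditional drug treatment will present distinct improvements in depression symptoms (MADRS". It adds that exercise with progressive motor complexity has not been tried before in this population.

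**The concern.** The paragraph prints a complete set of inputs and a result, so the result can be checked. If it does not follow from the inputs, the figure offered as the basis for the trial's size is wrong as written.

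The second question is what the 0.85 refers to. The effect size describes an aerobic program, whereas the stated objective sets one exercise program against another. If no AEMC-CAE difference entered the calculation, the article gives no power for that comparison. A reader who applied 0.85 to it could take a null AEMC-CAE result as more informative than it is.

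**Working it through.** **Inputs.** Effect size 0.25, power 0.85, alpha 0.05, correlation ρ = 0.8 and 21 per group, all from the power paragraph. Groups k = 3, measurements m = 2, Tukey after a significant F. Assumption: 0.25 is Cohen's f and the test is the group-by-time interaction.

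**Step 1: the plan's own figure.** For the interaction F-test, λ = f²·N·m/(1−ρ) = 0.0625 × N × 2 / 0.2 = 0.625·N, with (k−1)(m−1) = 2 and (N−k)(m−1) = N−3 degrees of freedom.

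| Total N | λ | df | Power |
|---|---|---|---|
| 20 | 12.5 | 2, 17 | 0.832 |
| 21 | 13.125 | 2, 18 | 0.854 |
| 63 (21 per group) | 39.375 | 2, 60 | 0.9999 |

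The smallest total that reaches 0.85 is exactly 21, or 7 per group. The stated 21 per group is not reproduced.

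**Step 2: other readings.**
- Between-groups main effect, f = 0.25, three groups: 161 in total, about 54 per group.
- Two-group interaction, or the within factor: 17 in total.
- Two-group t-tests with d = 0.25, one- or two-sided, on post-treatment, change or baseline-adjusted scores: 84 to 289 per group.
- A one-sided, two-group, baseline-adjusted test with d = 0.5 comes close (21 by normal approximation, 22 by exact t). It uses neither the stated effect size nor the three-group model.

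**Step 3: power for AEMC versus CAE.** No difference is stated, so power is shown over a range in units of the MADRS SD at one time point, taken as equal before and after. With two measurements, the group-by-time contrast is a comparison of change scores:

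- SD of change = SD·√(2(1−ρ)), which is 0.632 SD at ρ = 0.8 and 1.00 SD at ρ = 0.5.
- Noncentrality = (difference / SD of change)·√(n/2).
- Critical value = q(0.95; 3 means, 3(n−1) df)/√2, which is 2.403 at n = 21.

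Example: 0.50 SD, n = 21, ρ = 0.8 gives (0.50/0.632) × √10.5 = 2.56, and power 0.565.

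| AEMC-CAE difference | ρ = 0.8, 21 per group | ρ = 0.5 (assumed), 21 per group |
|---|---|---|
| 0.25 SD | 14% | 6% |
| 0.50 SD | 57% | 23% |
| 0.62 SD | 78% | 35% |
| Difference with 85% power | 0.67 SD | 1.07 SD |

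The article's allowance of 30% drop-out from 25 leaves 25 × 0.70 = 17.5, so 17 or 18 completers per group. The difference with 85% power is then 0.73-0.75 SD at ρ = 0.8, or 1.16-1.19 SD at ρ = 0.5. These powers are for the Tukey comparison alone; requiring a significant F first can only lower them.

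The 0.62 row is a yardstick: the Background says that two meta-analyses "reported that aerobic exercise can reduce depression symptoms (effect sizes of 0.62 and 0.56, respectively". Their metric is not stated, so the row does not predict the AEMC-CAE difference.

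**The case against.** The main counter-argument is that the slip, if it is one, errs on the safe side. The inputs need 21 patients for the overall test and 75 will be enrolled. This stands. A reader might infer that the error leaves the trial underpowered; for the omnibus group-by-time test that is not so.

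The reconstruction is also inferred. The article names neither f nor the interaction test. The exact match at 21 is strong evidence, but it is not proof that a total was copied as a per-group number. The authors should say which test they ran.

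A reader might further infer that 0.25 is an effect of exercise against no exercise. The text says only that an aerobic program can change MADRS. The comparator is not given, and a pre-post effect is possible. What can be said is that 0.25 is not stated to be an AEMC-CAE difference.

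The article never ties 0.85 to AEMC versus CAE in so many words, and its aims are mixed: the Abstract's Discussion stresses adding AEMC to drug treatment, and the hypothesis sentence closing the Background leaves out depression score. Even so, the Abstract and the Discussion both make AEMC against CAE on depression a purpose of the trial, and only one power figure is offered.

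Somewhat higher powers (15%, 62% and 82% at ρ = 0.8, with 85% at 0.64 SD) follow if MADRS is adjusted for baseline. The plan uses that analysis only if groups differ before the intervention, so the change-score figures fit the primary model.

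Finally, this is declared a superiority trial, and nothing in it says that a non-significant difference means equal effect. No disclaimer on that is asked for.

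**Conclusion.** The point holds in this form. Under the planned three-group, two-time model, with 0.25 read as f, 21 per group at power 0.85 does not follow from the stated inputs. The total is 21, and 21 per group would give 0.9999. This rests on an inferred metric and test; no other reading examined gives 21 per group under the planned model.

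Separately, and whichever test was used, 0.85 is not shown to be the power for AEMC versus CAE. At the article's own correlation and its expected 17-18 completers, 85% power needs a difference of 0.73-0.75 SD between two active programs. At an assumed correlation of 0.5 it needs 1.16-1.19 SD. These sizes assume change scores, equal SDs before and after, and Tukey over three pairs. They do not show that the true difference is smaller than that, only that the article gives no basis for claiming 85%.

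**What to change.** Keep 75 patients and reword the power paragraph:

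1. Name the test and the effect-size metric, and correct the sentence accordingly. If the calculation was the group-by-time F-test with f = 0.25, say that 21 is the total.
2. Do not attach 0.85 to AEMC versus CAE. State instead the AEMC-CAE difference detectable under the planned group-by-time analysis with Tukey, at the expected number of completers, for correlation 0.8 and for a lower assumed value. With 17-18 completers per group and 85% power, that is 0.73-0.75 SD at 0.8 and 1.16-1.19 SD at 0.5.

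The cost is a rewritten paragraph and a less favourable statement of power. No patients are added and the analysis does not change.
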